## Abstract

**Background:**

Hospital-acquired venous thromboembolism (HA-VTE) is a leading cause of morbidity and mortality among hospitalized adults. Numerous prognostic models have been developed to identify those patients with elevated risk of HA-VTE. None, however, has met the necessary criteria to guide clinical decision-making. This study outlines a protocol for refining and validating a general-purpose prognostic model for HA-VTE, designed for real-time automation within the electronic health record (EHR) system.

**Methods:**

A retrospective cohort of 132,561 inpatient encounters (89,586 individual patients) at a large academic medical center will be collected, along with clinical and demographic data available as part of routine care. Data for temporal, geographic, and domain external validation cohorts will also be collected. Logistic regression will be used to predict occurrence of HA-VTE during an inpatient encounter. Variables considered for model inclusion will be based on prior demonstrated association with HA-VTE and their availability in both retrospective EHR data and routine clinical care. Least absolute shrinkage and selection operator (LASSO) with tenfold cross-validation will be used for initial variable selection. Variables selected by the LASSO procedure, along with those deemed necessary by clinicians, will be used in an unpenalized multivariable logistic regression model. Discrimination and calibration will be reported for the derivation and validation cohorts. Discrimination will be measured using Harrell’s *C* statistic. Calibration will be measured using calibration intercept, calibration slope, Brier score, integrated calibration index, and visual examination of non-linear calibration curve. Model reporting will adhere to the Transparent Reporting of a multivariable prediction model for Individual Prognosis Or Diagnosis guidelines for clinical prediction models using machine learning methods (TRIPOD + AI).

**Discussion:**

We describe methods for developing, evaluating, and validating a prognostic model for HA-VTE using routinely collected EHR data. By combining best practices in statistical development and validation, knowledge engineering, and clinical domain knowledge, the resulting model should be well suited for real-time clinical implementation. Although this protocol describes our development of a model for HA-VTE, the general approach can be applied to other clinical outcomes.

**Supplementary Information:**

The online version contains supplementary material available at 10.1186/s41512-025-00205-8.

## Background

Venous thromboembolism (VTE) most frequently occurs among currently or recently hospitalized individuals [1]. Risk is known to vary by age and sex [1]. Despite increased awareness and efforts at prevention, VTE remains a leading cause of morbidity and mortality among hospitalized adults [2]. In the past 30 years, there have been no significant improvements in rates of VTE, and epidemiological studies suggest the overall incidence is increasing among an older population with a higher burden of comorbidities [3]. Currently available tools for predicting and preventing hospital-acquired VTE (HA-VTE) are limited in application to specific patient subpopulations (e.g., patients requiring medical care not in the intensive care unit, or patients undergoing scheduled surgery), provide overly broad categories for predicted risk based on dichotomized values for continuous risk factors (e.g., age, body mass index), and are difficult to automate in electronic health record (EHR) systems for use in real time [4–8]. Additionally, most of these models unfortunately have exhibited only modest prediction accuracy in derivation and validation cohorts, resulting in insufficient evidence to recommend the use of any specific model over others to guide clinical decision-making [9].

We previously developed and evaluated an initial prognostic model for HA-VTE in a derivation cohort of 132,365 patient encounters at the Vanderbilt University Medical Center (VUMC) adult hospital (1/1/2018–12/31/2020) [10]. While the development of this initial model was limited to demographic and clinical characteristics, diagnostic procedures, vital signs, and laboratory measurements, we demonstrated that such a model could perform well among the entire inpatient population, in contrast with other models that have been developed for specific patient populations. In this study, we will refine the model based on ongoing input from clinicians and consider additional risk factors for HA-VTE (e.g., medications, social determinants of health, environmental factors), with an eye toward real-time implementation. We will also perform additional external validation of the model to assess model generalizability.

Here, we outline the protocol for refining and validating a general-purpose prognostic model for HA-VTE designed for automated implementation within the EHR system. The target population includes all general adult patients admitted to the hospital. The model’s intended purpose is to calculate the predicted probability of HA-VTE for individual patients early in the hospital stay, and to guide HA-VTE prevention strategies. The scores will be made available to healthcare professionals. External validation of the model will be conducted across three distinct domains: temporal validation (in the same population in which the model was developed, but from a different calendar time), geographic validation (in a population different from the derivation population, but with similar characteristics), and domain validation (in a population with characteristics different from those in the derivation population). Model reporting will adhere to the Transparent Reporting of a multivariable prediction model for Individual Prognosis Or Diagnosis using machine learning methods (TRIPOD + AI) guidelines [11].

## Methods

### Setting

Model development and refinement will be performed using a derivation cohort of patients admitted to VUMC, a large academic medical center located in Nashville, TN. The derivation cohort consists of 132,561 inpatient encounters collected between 1/1/2018 and 12/31/2020. Temporal external validation will be conducted using a cohort of patients admitted to VUMC between 1/1/2021 and 10/21/2024. Geographic external validation will involve a cohort of patients admitted to Duke University Medical Center—a large academic medical center that serves a similar patient population as VUMC but in a different geographical location. Domain external validation will use a cohort of patients admitted to Vanderbilt regional hospitals that serve a distinct patient population. This study was approved by the Vanderbilt University Medical Center Institutional Review Board.

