### Model fairness

Model performance will be evaluated within patient subgroups defined by demographic characteristics, social vulnerability factors, and specific comorbidities. Variables across which model performance will be compared include patient age, sex, race, ethnicity, and cancer status. In addition to standard measures of discrimination, false-negative rates will also be compared across patient categories [16].

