### Statistical analysis

Patient encounter data will be summarized using median and interquartile range (IQR) for continuous variables and counts with percent for categorical variables. Encounter data will be summarized by cohort (derivation, temporal external validation, geographic external validation, and domain external validation) and by HA-VTE status. The rate of HA-VTE will be examined over continuous time and compared between cohorts. Statistical comparisons will be performed using chi-square tests for categorical variables and Kruskal–Wallis tests for continuous variables. A two-sided *p* value < 0.05 will indicate statistical significance. No adjustments will be made for multiple comparisons.

Model development will be performed within the derivation cohort described above. Data from validation cohorts will be kept fully external. Least absolute shrinkage and selection operator (LASSO) regression with tenfold cross-validation will be used for initial variable selection [19]. This will select the subgroup of variables minimizing cross-validation error. We will use the *C* statistic as the error measure to be optimized in the cross-validation process. LASSO variable selection will be performed using the “glmnet” package in R [20]. Restricted cubic splines will be considered for continuous variables. Variables selected in the LASSO procedure will be used in an unpenalized multivariable logistic regression model. Physician feedback regarding model complexity and variables necessary for inclusion will also be incorporated into the identification of the final prognostic model.

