Performance of the unpenalized logistic regression model, fit using variables selected in the cross-validation procedure, as well as any additional variables identified by clinicians as necessary for clinical validity, will be reported in the derivation cohort as well as the temporal, domain, and geographic external validation cohorts. More complex models, such as random forest or XGBoost, will not be considered as there was minimal to no improvement in performance when using these models compared to logistic regression (data not shown). Predicted probabilities for each patient will be generated using the fitted logistic regression model object and the *predict()* function in R. Prediction performance will be quantified using measures of discrimination (*C* statistic [21]), calibration (calibration intercept, calibration slope, Brier score, integrated calibration index, and visual examination of non-parametric calibration curve), and distribution of predicted risk [22–24]. Model variable importance and odds ratios with 95% CI will be reported. Additionally, we will report model performance within pre-specified subgroups. Predictions in the external cohorts will be generated using the non-recalibrated model. Models with recalibrated coefficients may be considered if there is a substantial decrement in prediction performance. In such cases, recalibrated and non-recalibrated model performance will be reported and compared. We will follow TRIPOD + AI guidelines [11] for model reporting. All analyses will be conducted using the current version of R statistical software [25].

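### Domain validation is described as one cohort over several regional hospitals with no hospital-level results, so pooled calibration could dilute, or with offsetting errors hide, miscalibration at individual hospitals

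*Protocol article*

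**What the plan says.** All references are to the protocol article.

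- **Source of the cohort (Methods, Setting).** "Domain external validation will use a cohort of patients admitted to Vanderbilt regional hospitals that serve a distinct patient population". The hospitals are plural and the cohort is single. The temporal and geographic cohorts each come from one named medical centre.
- **Role of the cohort (Background).** Domain validation is defined as validation in a population whose characteristics differ from those of the derivation population. Neither of the other two external validations is defined that way.
- **Unit of description (Statistical analysis).** "Encounter data will be summarized by cohort (derivation, temporal external validation, geographic external validation, and domain external validation) and by HA-VTE status".
- **Unit of evaluation (Statistical analysis).** Performance "will be reported in the derivation cohort as well as the temporal, domain, and geographic external validation cohorts". The calibration measures are "calibration (calibration intercept, calibration slope, Brier score, integrated calibration index, and visual examination of non-parametric calibration curve".
- **Subgroups (Model fairness).** The axes are demographic characteristics, social vulnerability and comorbidities: "Variables across which model performance will be compared include patient age, sex, race, ethnicity, and cancer status". Statistical analysis adds: "Additionally, we will report model performance within pre-specified subgroups". It does not list those subgroups.
- **Recalibration (Statistical analysis).** "Predictions in the external cohorts will be generated using the non-recalibrated model". Then: "Models with recalibrated coefficients may be considered if there is a substantial decrement in prediction performance". No threshold is given.

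**The concern.** The score is meant to give an individual probability early in the stay and to guide prevention. For any patient, what matters is whether that probability is right at the hospital where the patient lies. A calibration intercept, slope or integrated calibration index (ICI) taken over several hospitals is a size-weighted and risk-weighted average. If the model under-predicts at one hospital and over-predicts at another, the average can look better than either.

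Some difference between hospitals is plausible on the article's own account. The limitations section says that thromboprophylaxis can influence calibration and discrimination, and that it is deliberately not modelled. It also says that the ICD-based outcome may be misclassified. Neither statement shows that the regional hospitals do differ.

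Two things are at stake: how the one validation in a dissimilar population is read, and the decision to recalibrate. If that decision rests on pooled figures, a local error could pass unnoticed.

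**Working it through.** **What can be reproduced.** The article gives no hospital count, hospital size, event rate or calibration target for the domain cohort. There is no stated figure to reproduce, and the actual size of any masking cannot be derived. What follows shows only what pooling can and cannot hide. Every numerical input is an assumption.

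**Formula.** Let hospital *h* have *n_h* encounters, mean predicted risk *p_h* and ratio *OE_h* of observed to expected events. Then

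pooled O/E = Σ(n_h × p_h × OE_h) / Σ(n_h × p_h).

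With equal mean predicted risk, this is the size-weighted mean of the hospital ratios.

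**Common inputs for cases 1 to 4 (assumed).** The linear predictor is normal with mean −4.8 and SD 1.0 at every hospital, so mean predicted risk is about 1.31%. A hospital's error is a shift of the true log-odds. The pooled slope comes from a logistic model of the outcome on the linear predictor, evaluated by numerical integration.

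1. *Equal sizes, offsetting errors.* Shifts of +0.23 and −0.30 give O/E of 1.25 and 0.75. Pooled O/E = (1.25 + 0.75)/2 = 1.00, fitted intercept −0.01, slope 0.998. The pooled figures show nothing.
2. *Sizes 3:1, offsetting errors.* O/E of 1.1 and 0.7: (3 × 1.1 + 0.7)/4 = 1.00, slope 0.999. Equal size is therefore not needed for masking.
3. *Sizes 3:1, error at the smaller hospital only.* O/E of 1.0 and 0.5: (3 × 1.0 + 0.5)/4 = 0.875, slope 0.998. Twofold over-prediction at the smaller hospital appears as a mild overall shift. This is dilution, not cancellation.
4. *Sizes 3:1, errors that do not balance.* O/E of 1.25 and 0.75: (3 × 1.25 + 0.75)/4 = 1.125. With the sizes reversed: (1.25 + 3 × 0.75)/4 = 0.875. The pooled result shows part of the error.

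**Second illustration (assumed).** This was simulated with SD 1.2, 400,000 encounters per hospital and mean risk about 1%, except that case mix differs in the last row.

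| Hospitals (target O/E) | Hospital results | Pooled results |
|---|---|---|
| Two equal: 1.5, 0.5 | intercepts +0.42 and −0.70; ICI 0.0049 each | O/E 1.00, intercept −0.002, slope 0.99, ICI 0.0001 |
| Three equal: 1.5, 1.5, 0.5 | intercepts +0.43, +0.44, −0.69 | O/E 1.18, intercept +0.17, slope 0.99, ICI 0.0018 |
| Two with different case mix: 1.5 (lower risk), 0.75 (higher risk) | intercepts +0.42 and −0.31; slopes 1.01 and 0.99 | O/E 0.95, intercept −0.06, slope 0.86 |

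In the first row the pooled measures are nearly perfect while both hospitals are badly calibrated. In the second row the pooled intercept gives the problem away in part. In the third row the pooled slope does, although the slope is about 1 at each hospital. In all three, hospital-level results show the error directly.

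**The case against.** **Silence is not refusal.** The article nowhere says that hospital-level results will be withheld. The list of comparison variables is open-ended, the pre-specified subgroups are not enumerated in Statistical analysis, and a fuller plan may report by hospital. This stands as a limit on how strongly the point can be put. It does not remove the point, because the article does state its unit of evaluation, which is the cohort, and the subgroup categories it names do not cover hospital.

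**Cancellation is a special case.** Case 1 was chosen so that the errors offset, with identical case mix. This stands too. Case 4 and the last two rows of the table show that unbalanced errors or differing case mix leave a trace in the pooled intercept or slope. Errors in the same direction at all hospitals would show fully. Case 3 nevertheless shows that dilution needs no offsetting errors.

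**Stronger readings that do not hold.** A reader might infer that miscalibration will cancel, that the model will be declared transportable, or that it will be wrong at every hospital. The article supports none of these. It sets no acceptance rule and says only that validation will assess generalizability. Nor does its remark that Braden scores are recorded according to hospital policy show that policy differs between hospitals.

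**Other evidence and use.** Temporal and geographic validation also bear on generalizability, and each uses a single named centre. The article does not say at which hospitals the score will be deployed. Both points are fair. They limit the consequence, but they do not supply the missing view of the regional hospitals.

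**Conclusion.** The point holds in a limited form. As described, the only validation in a dissimilar population is evaluated as one unit across several hospitals, and that unit can dilute or hide hospital-level miscalibration. Under the assumed inputs, the pooled O/E ranges from 1.00 (errors of 25% in opposite directions, fully hidden) to 0.875 (one hospital over-predicted twofold, shown as a mild shift). Where errors are unbalanced or case mix differs, part of the problem remains visible: a pooled O/E of 1.125 or an intercept of +0.17 in the first situation, a slope of 0.86 in the second.

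These figures show what is possible and do not estimate what will happen. The conclusion rests on the hospitals differing materially, which the article neither asserts nor rules out, and on the cohort being the only reporting unit, which is what the article describes. It is a worthwhile, low-cost improvement, not an error that invalidates the validation.

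**What to change.** In Statistical analysis, keep the pooled domain results and add:

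- the C statistic, calibration intercept, calibration slope and calibration curve for each regional hospital, with 95% CIs;
- a rule, fixed before the data are examined, for grouping very small hospitals;
- a description of the between-hospital spread, such as a forest plot or the range of intercepts and slopes, with a random-effects summary only if there are enough hospitals to support one;
- a statement that hospital-level results will be consulted before any decision on recalibration in the domain cohort.

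The cost is one extra table or plot, and a hospital identifier must be kept in the analysis file. The drawback is wider intervals at hospitals with few events, so single-hospital estimates should be read with their intervals and not as pass or fail.

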### Population

We will include all adult inpatient encounters occurring during the specified locations and timeframes. All patients admitted to the adult inpatient setting over the age of 16 years will be included. Exclusion criteria are kept purposely minimal to maximize generalizability.

### Data sources

Integrating prediction models into clinical workflows requires consistent data definitions between the data used for model development and the data used for real-time implementation. To ensure that the retrospective data extracted for model development aligned with the data available during real-time use, we adopted knowledge engineering best practices. These practices allowed us to accurately represent the clinical concepts to be used by the model and included steps for data coverage analysis and validation.

First, we represented the clinical concepts of interest using standards-based value sets, incorporating applicable standard terminologies such as LOINC, SNOMED, and RxNorm. Each clinical concept to be referenced in the model was defined using these terminologies to ensure standardization. Next, we analyzed the local EHR build to evaluate the coverage of the concepts represented by the standards-based value sets. During this process, any gaps were addressed by augmenting the value sets with local extensions, such as EHR-specific identifiers. Finally, we collaborated with clinical subject-matter experts in a validation step to ensure that the identified concepts accurately captured their intended clinical definitions. Once validated, the value sets were enhanced with appropriate metadata to facilitate ongoing lifecycle management.

These best practices improve consistency between the developed model and its real-time implementation, while enabling semantic interoperability by utilizing standards-based concept representation.

### Potential predictors

A fixed set of candidate predictors for potential inclusion in the prognostic model for HA-VTE has been defined. Variables included as candidate predictors were based on prior demonstrated association with HA-VTE and their availability in both retrospective EHR data and routine clinical care. Candidate predictor categories include demographic characteristics and social determinants of health (e.g., age, sex, race, and ethnicity), inpatient encounter details (e.g., admission type), medical history that is either active or diagnosed during the encounter (e.g., Elixhauser comorbidity details [12], prior history of VTE), vital signs, laboratory measurements, medications (e.g., immunoglobulins, glucocorticoids, statins), nurse-recorded information regarding mobility (e.g., Braden sub-scores, Richmond Agitation-Sedation Scale (RASS) score [13]), and environmental factors. Braden and RASS scores are routinely documented in the nursing flowsheet, with Braden scores typically recorded every shift per hospital policy. A full list of variables and their definitions are provided in the appendix (see Additional file 1). Indicator variables will be created for whether medications within each category were active at admission and administered during the encounter. These variables will be considered separately during the model-development process. Environmental factors include the Neighborhood Atlas’s rankings on socioeconomic disadvantage [14] and air quality, as captured by the Environmental Protection Agency’s air quality index [15]. These community-level factors will be linked to patients based on their admission date and home ZIP code. Distributions of continuous variables will be examined for clinically implausible values. Such values will be treated as missing.

### Outcomes

The primary outcome will be the development of any non-superficial VTE during the course of the inpatient encounter. This outcome will be modeled as a binary variable. The time horizon for prediction begins at hospital admission and continues until discharge. Presence of HA-VTE will be defined using ICD-10 diagnosis codes (see appendix). ICD-based outcome definitions are applied consistently across all patients. In a manual retrospective review of 120 randomly selected HA-VTE cases defined using ICD-based identification, each case was confirmed to be a correct diagnosis [10]. VTE diagnosis codes flagged as present on admission will be excluded from the outcome definition. Clinical subtypes of HA-VTE (e.g., location and severity) will be reported. Subtype-specific predictions will not be obtained. Prior diagnosis of VTE will be used to indicate history of VTE and included as a potential predictor.

